### Secondary study questions

2. Is there any relation between the results of the preventive health examinations and the RI-DP Index (traffic light systems)?3. Is there any relation between the results of the questionnaire survey and the RI-DP Index (traffic light systems)?4. What is the general health status of the sample of German employees aged 45–59?5. Which diseases are most common in the sample?6. What is the general health status of specific occupational groups?

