### Risk index – Disability pension

The study of the RI-DP was designed as a case–control study of the GPF using data from 8,500 men and 8,405 women. Independent samples (control group) were used to validate their models. The information revealed by that index can be used to enhance the provision of rehabilitation programs. The RI-DP can be calculated based on secondary data for the 3 years preceding the reference year. A person has a high risk of disability pension if the RI-DP is ≥60, a moderate risk is <60 und ≥ 50, and a low risk is <50 (16, 19).

In our study, the RI-DP is collected and considered during recruitment. It does not influence the study participation or non-participation. Physicians and study participants do not have any information about the respective index value (of the subject), only the project management does.

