## Statistical methods

All analyses will be conducted in an explorative setting. In the first step, a descriptive analysis will be performed summarizing all variables with absolute and relative frequencies for categorical variables, and means and standard deviations for continuous variables. Based on the primary study question, the hypothesis is that the assessment based on preventive health examinations differs from the assessment according to the Ü45-questionnaire. Hence, for the primary endpoint, the score according to the Ü45-Screening questionnaire will be evaluated first. Afterward, the results of the classification of patients into green, yellow and red based on the Ü45-Screening questionnaire are compared with the classification according to the physician’s assessment. Therefore a Stuart-Maxwell test will be used to test for marginal homogeneity and a weighted kappa coefficient using linear weights will be calculated. In the second step, the differences between the results based on the Ü45-Screening questionnaire and the medical assessment will be visualized using boxplots and histograms for all variables based on the clinical examination and the questionnaire, respectively. In addition, these variables are used to build two ordinal regression models, one that uses the physician’s assessment as the dependent variable and one with the assessment by the Ü45-Screening questionnaire as the dependent variable. In each case, the green category is used as a reference. The two regression models are compared to determine the factors influencing the various ratings. Secondary aims (2) and (3), which aim to compare the assessment by means of the Ü45-Screening questionnaire and the medical assessment with the RI-DP index, respectively, will also be assessed by visualization for all variables using boxplots and histograms. Since the RI-DP index measures a different outcome from the assessment by the Ü45-Screening questionnaire and the medical assessment, a statistical test will not be used.

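### Study questions 2 and 3 ask whether a relation with the RI-DP exists, but only plots are planned, and the reason given for omitting a test excludes agreement methods, not association methods

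*Protocol article*

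**What the plan says.** The section Secondary study questions words both aims as questions about a relation. Question 2: "Is there any relation between the results of the preventive health examinations and the RI-DP Index (traffic light systems". Question 3: "Is there any relation between the results of the questionnaire survey and the RI-DP Index (traffic light systems".

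The Statistical methods section says that these two aims "will also be assessed by visualization for all variables using boxplots and histograms". It then gives a reason for going no further: the index "measures a different outcome from the assessment by the Ü45-Screening questionnaire and the medical assessment, a statistical test will not be used". No cross-tabulation with the RI-DP, association measure or confidence interval is named for either aim.

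Three other statements bear on the point:

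- The primary question, which compares the two instruments with each other, does get statistics: "Therefore a Stuart-Maxwell test will be used to test for marginal homogeneity and a weighted kappa coefficient using linear weights will be calculated".
- The whole plan is declared exploratory: "All analyses will be conducted in an explorative setting". A general first step is also planned: "a descriptive analysis will be performed summarizing all variables with absolute and relative frequencies for categorical variables".
- The RI-DP is a numeric score cut into three ordered classes: below 50, 50 to below 60, and at the top "A person has a high risk of disability pension if the RI-DP is ≥60".

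**The concern.** The stated reason runs together two kinds of analysis. Agreement methods ask whether two ratings give the same answer, so they need both ratings to measure the same thing. Association methods ask whether one quantity tends to rise with another, and they make no such demand. Questions 2 and 3 are of the second kind. The argument that the outcomes differ therefore justifies leaving out kappa and Stuart-Maxwell, but not an association estimate.

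This is a stated decision with a stated reason, not a detail that an article leaves to a fuller plan.

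At stake is what the study can report on two of its own six questions. The RI-DP comes from register data and is withheld from physicians and participants, so it is a comparator independent of both instruments. With plots alone, the reader gets a visual impression with no size and no uncertainty. Boxplots and histograms are also a poor display for two three-level classifications.

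**Working it through.** **Which methods the reason excludes**

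| Method | Needs the same outcome on both sides? | Excluded by the stated reason? |
|---|---|---|
| Weighted kappa | Yes | Yes |
| Stuart-Maxwell (equal margins) | Yes | Yes |
| Rank correlation, tau-b | No | No |
| Ordinal regression on the RI-DP score | No | No |
| 3x3 table with percentages | No | No |

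**Inputs for an illustration of precision**

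- n = 1,000, the lower bound of the target (Study design and population).
- n = 660, screened by April 2023 (Trial registration and status).
- The documents give no alpha, power or effect size for these aims, so there is no figure to reproduce. A two-sided 5% level, 80% power and the correlations below are assumptions.

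**Step 1: interval width.** Fisher-z interval for a Spearman correlation: tanh(atanh(r) ± 1.96·SE), with SE = √((1 + r²/2)/(n − 3)).

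For r = 0.20 and n = 1,000: SE = √(1.02/997) = 0.032, atanh(0.20) = 0.203, and the limits are tanh(0.203 ± 0.063) = 0.14 and 0.26.

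| Assumed r | 95% CI, n = 1,000 | 95% CI, n = 660 |
|---|---|---|
| 0 | −0.06 to 0.06 | −0.08 to 0.08 |
| 0.1 | 0.04 to 0.16 | 0.02 to 0.18 |
| 0.2 | 0.14 to 0.26 | 0.13 to 0.27 |
| 0.3 | 0.24 to 0.36 | 0.23 to 0.37 |

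**Step 2: smallest detectable correlation.** tanh((1.96 + 0.84)/√(n − 3)) gives 0.09 at n = 1,000 and 0.11 at n = 660.

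**Step 3: three-level ratings with different margins.** Steps 1 and 2 ignore the ties that three-level ratings create. A simulation with 1,000 runs per setting used two three-level variables with deliberately different margins (1/3, 1/3, 1/3 against 0.50, 0.35, 0.15) and a Kendall tau-b test at 5%.

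| Latent correlation | Rejected, n = 1,000 | Rejected, n = 660 | Mean tau-b (SD), n = 1,000 |
|---|---|---|---|
| 0 | 4.9% | 4.3% | 0.00 (0.028) |
| 0.1 | 67.6% | 52.2% | 0.07 (0.029) |
| 0.2 | 100% | 98.4% | 0.14 (0.027) |

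The Monte Carlo standard error at 5% is √(0.05·0.95/1,000) = 0.7 points, so both false-positive rates are compatible with 5%. Different margins do not invalidate the test. At a latent correlation of 0.2 and n = 1,000, tau-b would be known to about 0.14 ± 1.96·0.027, or 0.09 to 0.19. At 0.1, detection is far from certain once both variables are cut into three classes, which favours using the numeric RI-DP score.

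**Step 4: the sampling design.** Participants are drawn from each of the three RI-DP groups. A pooled rank correlation or tau-b therefore depends on how many come from each group. The distribution of the traffic light given the RI-DP does not, as far as this sampling step goes. Percentages within RI-DP group and a regression of the traffic light on the RI-DP are thus the safer summaries.

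**The case against.** The strongest reply is that the study is openly exploratory, these aims are secondary, and the abstract words them as comparisons. Omitting p-values is then defensible, and a plot of the RI-DP score by traffic-light colour does give an informal answer. That stands, and it limits the point to the missing estimate and interval. It does not rescue the stated reason. The primary question is equally exploratory and still gets a test and a coefficient.

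A reader might infer several stronger claims that the document does not support:

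- **That every statistic is refused.** The text excludes a test. An association coefficient is left out, not forbidden, and descriptive summaries of all variables are planned.
- **That the questions cannot be answered at all.** They can be answered informally, but not with a size and an uncertainty.
- **That the plots certainly omit the classifications.** The phrase about all variables may mean only the single measurements or may include the colours. The sentence is ambiguous.
- **That the ordinal regressions in the same section contradict the stated reason.** The physician's rating is formed from the history and examination results (Traffic light system), so modelling it on examination variables largely explains a rating by its own inputs. Relating it to an index that the physician never sees is a different exercise.
- **That the RI-DP would settle which instrument is better.** It is a prediction index, not observed disability pension, and the study questions do not ask for such a ranking.

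**Conclusion.** The point holds in this form: the plan asks about a relation, names only plots, and justifies omitting a test by an argument that applies to agreement, not association. As written, neither question gets a quantified answer with uncertainty.

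The achievable precision is good: about ±0.06 around a rank correlation at n = 1,000 and about ±0.08 at n = 660. These figures rest on assumed correlations and on a formula that ignores ties and the sampling by RI-DP group, so they show only the order of magnitude.

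This should be fixed. A higher grade is not warranted, because the aims are secondary and exploratory and the primary analysis does not depend on them.

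**What to change.** Replace the exclusion sentence with a statement that, because the RI-DP measures a different outcome, no agreement or marginal-homogeneity statistic will be used for aims 2 and 3. Then, for each instrument, specify the following, labelled exploratory:

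1. The 3x3 table of traffic light by RI-DP group, with percentages within RI-DP group.
2. A cumulative-logit regression of the traffic light on the RI-DP score: logit P(Y ≥ k) = α_k + β·(RI-DP/10), for k = yellow and red. Report OR = exp(β) per 10 points with 95% CI. Ten points is the width of the moderate-risk band (60 − 50). Check proportional odds and linearity.

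Regressing on the RI-DP conditions on the sampling variable, but it does not remove self-selection. Attendance is voluntary, and the Limitations section says it may depend on feeling worse or on having more risk factors. State this beside the estimate. Report any pooled tau-b or Spearman coefficient only with the caveat that it depends on the mix of RI-DP groups. A paired comparison of the two instruments is optional. The plots can stay.

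While editing, correct the order in the sentence on aims 2 and 3. It pairs them with questionnaire and medical assessment respectively, the reverse of the Secondary study questions section.

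The cost is a few lines of text and code, plus some additional exploratory estimates to interpret. The RI-DP value is already held by the project management, so no new measurements are needed. By the article's dates, recruitment runs to March 31, 2024, so the article's timetable leaves room to change the plan before the final analysis.

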### Preventive health examination

The health professionals at Charité – Universitätsmedizin Berlin will perform the clinical examination. The examination in total takes approximately 120 min including the following diagnostics: Anthropometric measurements, bioelectrical impedance analysis (BIA), handgrip strength, systolic and diastolic blood pressure (SBP and DBP) (25), resting electrocardiogram (ECG), and pulse wave velocity (PWV) (26). The subjects will wear underwear during instrumental diagnostics.

Details about the diagnostics and measurements are given in Table 2.

**Table 2 tab2:** Measurements in preventive health examination Ü45-Check.

Clinical measures	Measurement	Technical information
Anthropometry	**Height (cm), Weight (kg)** Body-Mass-Index (BMI) (kg/m^2^)	Seca 274 Stadiometer, Seca, Germany
	**Waist (cm), Hip (cm)** Waist-to-Hip-Ratio (WHR) (Waist cm/Hip cm)	Seca 201 measuring band, Seca, Germany
Body composition	**Bioelectrical Impedance Analysis (BIA)** Percent body fat (PBF), Fat free mass (FFM), Visceral fat area (VFA), Total body water (TBW), Intracellular water (ICW), Extracellular water (ECW), Phase angle (PhA)	InBody 770, Inbody, South Korea
Handgrip strength diagnostics	**Handgrip Strength** (2 times each hand)	Hand dynamometer Lite, Baseline Evaluation Instruments, Germany
Cardiovascular diagnostics	**Twelve-lead Resting Electrocardiogram (ECG)**	Custo cardio 400, Custo med, Germany
Vascular diagnostics	**Blood Pressure (BP)** Systolic blood pressure (SBP) Diastolic blood pressure (DBP)	Classic III Stethoscope, 3 M Littmann, U.S.; boso med I, BOSCH + SOHN GmbH, Germany
	**Pulse Wave Velocity (PWV)** **Pulse Wave Analysis (PWA)**	Vicorder, SMT, Germany
Anamnesis	Chronic or current symptoms, medical history, family history, medication, dietary habits/supplements Cardiovascular risk factors, activity and training	IPAD 6th generation, Apple, U.S.
Cardiovascular examination	Cardiac examination Pulmonary examination Abdominal examination Peripheral vascular Examination	CORE Digital-Stethoscope, 3 M Littmann, U.S.
Blood sampling and analyses	**Blood Analyses** Blood cell and differential cells count, electrolytes, C-reactive protein (CRP), liver enzymes (GOT (AST), GPT (ALT), gamma-GT), blood lipid levels (total cholesterol, HDL-cholesterol, LDL-cholesterol and triglycerides), renal function parameters, ferritin, fasting glucose, Glycosylated hemoglobin (HbA1C), thyroid-stimulating hormone (TSH), urine test strip	

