In order to assess the general health status of the sample, the variables of the anamnesis and the clinical examination are of main interest. Those variables are analyzed descriptively with absolute and relative frequencies for categorical variables, and means and standard deviations for continuous variables. In addition, this is also conducted as a subgroup analysis for different occupations. In order to assess which diseases are the most common in the sample, the absolute and relative frequencies of each disease are calculated and compared.

If missing values are present, their structure is analyzed and based on this, multiple imputation is considered.

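### Mean and SD are the only numerical summaries prescribed for continuous variables, which can misstate the typical value of strongly skewed laboratory markers in the tables for questions 4 and 6

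*Protocol article*

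**What the plan says.** The Statistical methods section of the protocol article states the rule twice. The general first step reads: "a descriptive analysis will be performed summarizing all variables with absolute and relative frequencies for categorical variables, and means and standard deviations for continuous variables". For question 4 the section says that "the variables of the anamnesis and the clinical examination are of main interest", and then: "Those variables are analyzed descriptively with absolute and relative frequencies for categorical variables, and means and standard deviations for continuous variables". The next sentence extends this to a subgroup analysis by occupation, which is how question 6 is answered.

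Table 2 (Preventive health examination) lists the affected measurements among the clinical measures. They include "C-reactive protein (CRP), liver enzymes (GOT (AST), GPT (ALT), gamma-GT" and, further along the same row, "LDL-cholesterol and triglycerides), renal function parameters, ferritin".

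The section also plans graphs. Differences between the questionnaire and the physician's assessment are to be "visualized using boxplots and histograms for all variables based on the clinical examination and the questionnaire, respectively". The same kinds of graph are planned for aims 2 and 3, the comparisons with the RI-DP. Neither sentence mentions question 4 or occupations. The section opens with: "All analyses will be conducted in an explorative setting".

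**The concern.** The article names a summary statistic and names no other, so this is a stated rule and not a silence for an analysis plan to fill. An analysis plan that replaced the mean by the median would depart from the published wording.

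The markers concerned cannot be negative and can have long upper tails. For such a variable the mean is pulled upwards by a minority of high values. It then no longer describes a typical participant, and the SD says little about where most values lie.

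For continuous variables in questions 4 and 6 there is no model or test behind the summary: the table entry is the result. In the occupational tables a few high values, or even one, could make a group look different from the others.

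**Working it through.** The plan has no figure of its own to reproduce. The article gives no mean, SD, median or skewness for any laboratory value, and no occupational group sizes. The calculations below are illustrations over assumed inputs.

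**Step 1. Mean against median in a skewed variable.** Assume a lognormal variable with median 1 and log-SD s. Then:

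- mean/median = exp(s²/2)
- share of people below the mean = Φ(s/2)
- SD/mean = √(exp(s²) − 1)

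| s (assumed) | mean/median | share below the mean | SD/mean | (mean − 1 SD)/mean | (mean − 2 SD)/mean |
|---|---|---|---|---|---|
| 0.5 | exp(0.125) = 1.13 | Φ(0.25) = 60% | 0.53 | 0.47 | −0.07 |
| 0.75 | exp(0.281) = 1.32 | Φ(0.375) = 65% | 0.87 | 0.13 | −0.74 |
| 1.0 | exp(0.5) = 1.65 | Φ(0.5) = 69% | 1.31 | −0.31 | −1.62 |

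**Step 2. How far this depends on the degree of skew.** Written in terms of the coefficient of variation (CV), mean/median = √(1 + CV²):

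- CV 0.3: √1.09 = 1.04
- CV 0.5: √1.25 = 1.12
- CV 1.0: √2 = 1.41
- CV 1.5: √3.25 = 1.80

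The distortion is negligible for mildly skewed variables and material only for strongly skewed ones.

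**Step 3. One extreme value in a subgroup.** Assume an occupational group of 20, with 19 CRP values of 1 mg/L and one acute value of 50 mg/L. The mean is (19 × 1 + 50)/20 = 69/20 = 3.45, and the median stays at 1. With 660 people, the number examined by April 2023, the same single value gives (659 + 50)/660 = 1.07. The sensitivity to one person is therefore a subgroup problem much more than a whole-sample one.

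**Step 4. Do the planned graphs fill the gap?** Boxplots show medians and quartiles, and histograms show skew. They are planned for all clinical examination and questionnaire variables, but to display the questionnaire-versus-physician comparison and the two RI-DP comparisons. The text on questions 4 and 6 names frequencies, means and SDs only. The graphs would reveal skew to the analysts, but as written they are not part of the answer to these two questions.

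**The case against.** The strongest reply is that this is ordinary analysis-plan detail. A generic sentence on descriptive statistics in a condensed article does not forbid adding medians, and mean and SD are valid descriptive statistics. It is true that nothing is contradicted and that the summary is incomplete rather than wrong. The reply does not remove the point, because the article fixes a choice, repeats it, and makes no exception.

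A second reply is that the boxplots and histograms will show the distributions. That holds for the rating and RI-DP comparisons and only in part for questions 4 and 6.

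Third, the stakes are limited. Question 4 is also answered by frequencies of categorical findings and by measures not challenged here, such as blood pressure, body composition and grip strength. No test between occupations is described, and all analyses are exploratory. This stands, and it lowers the weight of the point.

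Three stronger readings are tempting, and the documents do not support them:

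- A reader might infer that question 4 will report misleading values. The article gives no distributions, so only the possibility is shown, and only for strongly skewed markers.
- A reader might infer that false occupational differences are likely. No group sizes are given, and the group of 20 above is an assumption. Likewise, a negative mean minus 2 SD matters only to someone who builds a range from it, and the plan does not.
- A reader might infer that the same markers must be log-transformed in the ordinal regression models. Those models do not require normally distributed covariates, so this does not follow from a point about summary tables.

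**Conclusion.** The point holds with low severity. The article prescribes mean and SD as the sole numerical summary for every continuous variable, including the tables for general health status and for occupational groups. For strongly right-skewed markers in Table 2 this can overstate the typical value, by a factor of 1.13 to 1.65 for log-SDs of 0.5 to 1.0.

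That range rests on an assumed lognormal shape and assumed log-SDs. The effect in small groups rests on an assumed group size. It also rests on the blood values counting as part of the clinical examination for question 4. The heading of Table 2 and the general rule covering all variables make that the natural reading, although the text on question 4 does not say so outright.

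The comparison of questionnaire and physician ratings by the Stuart-Maxwell test and weighted kappa is not affected.

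**What to change.** Amend both sentences on continuous variables in the Statistical methods section. Skewed continuous variables should be summarised by median and quartiles, alone or beside mean and SD, in the overall and the occupational tables. Mean and SD stay for roughly symmetric variables. Name the variables in advance, for example CRP, ferritin, triglycerides and gamma-GT. Giving both summaries for every continuous variable would avoid a choice made after seeing the data.

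As an option, add the number and share of participants outside the laboratory's reference limits, which bears directly on health status.

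The cost is a short change of wording and slightly longer tables. Data collection, sample size and the primary analysis do not change.

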### Ethics approval and consent to participate

Ethics approval was obtained by the “Ethics Committee of the Faculty of Culture, Social and Educational Sciences, Humboldt-Universität zu Berlin” on August 20, 2020 (reference number: HU-KSBF-EK_2020_0010). The work described is carried out in accordance with the Declaration of Helsinki for experiments involving humans. All subjects are informed by the study staff about the study procedure, subsequent data storage, and confidentiality and pseudonymity regarding the data. Written informed consent is collected from all subjects that the study center is allowed to use the data for research analyses and publishing the data.

